### Sample size calculation

2.6

The sample size calculation was performed using PASS 15.0.5 software (NCSS, LLC). The estimation was based on the change in the 8-week Montreal Cognitive Assessment (MoCA) score post-treatment. Previous studies (17, 18) reported a total effective rate of 13.72% for the 8-week MoCA score in the sham acupuncture group after treatment. We anticipated a total effective rate of 58.33% for the 8-week MoCA score post-treatment in the verum acupuncture group. With a significance level of *α* = 0.05 (two-sided) and a power of 0.9, accounting for a 20% attrition rate, and an equal 1:1 group allocation, a minimum of 25 cases per group were determined necessary. Consequently, this study requires a total of 50 participants.

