#### Primary indicator

2.7.1

The primary outcome measure is the total effective rate of the 8-week MoCA score. Changes in the MoCA score from baseline to the end of treatment and the follow-up period will assess patients’ cognitive function. The MoCA, a concise cognitive function assessment tool comprising 12 items, was developed by Nasreddine in 2005. It evaluates visuospatial abilities, executive function, short-term memory, language, and orientation to time and place (19). The MoCA test has a maximum score of 30 points, with scores between 21 and 26 indicating mild cognitive impairment. For individuals with 12 or fewer years of education, one point is added to the final score (37). The lower the score, the worse the cognitive function. To evaluate cognitive function, the MoCA score and total improvement rate will be assessed at baseline, at the conclusion of treatment, and during the follow-up period. The score of the MoCA, the absolute changes in scores from baseline to the end of treatment, and the follow-up period will be recorded. The minimum clinically significant difference of MoCA is 1.22 points (38). Improvement rate = [(posttreatment score − pretreatment score)/pretreatment score] × 100%. The curative effect is judged as follows: Significantly effective: Improvement rate≥20%; Effective: 12% ≤ Improvement rate<20%; Invalid: −12% ≤ Improvement rate<12%; Total effective rate according to the formula: (Significantly effective + Effective)/Total cases×100%.

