## Statistical analysis

4

The statistical analysis will be conducted using Microsoft Excel 2016 and SPSS 25.0 statistical software (IBM Corporation, Armonk, NY, United States). An independent statistician, blinded to group assignment, will perform the statistical analysis. All data will be analyzed according to the intention-to-treat (ITT) protocol, regardless of adherence, provided participants receive at least one acupuncture treatment session and complete a baseline assessment of the primary outcome. Missing values will be imputed using the last observation carried forward method. The per-protocol (PP) population, comprising all randomized patients who completed more than 80% of the treatment procedure, will also be analyzed. All statistical tests will be two-sided, with a *p* value of <0.05 considered statistically significant. Categorical variables will be reported as medians (interquartile ranges), while continuous variables with normal distributions will be presented as means ± standard deviations. The chi-square test or Fisher’s exact test will be employed to compare dichotomous data from baseline demographic and clinical information. Measurement data include various scale scores and indicators of inflammatory cytokine expression levels. For normally distributed variables, an independent samples t-test will be used for between-group comparisons, and a paired samples t-test for within-group comparisons before and after therapy. Comparisons at multiple time points will be made using repeated-measures analysis of variance. The Mann–Whitney U test will be utilized for non-normally distributed variables in intergroup comparisons to analyze changes in efficacy outcomes. The comparison of multiple time points will be based on the generalized estimating equation (GEE). Multiple linear regression analysis will be employed to examine correlations between clinical efficacy and inflammatory cytokines.

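### The analysis section assigns no between-group test to the responder-rate primary endpoint, and, as a separate matter, names the baseline score as a covariate in no efficacy comparison

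*Protocol article*

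**What the plan says.** Section 2.7.1 (Primary indicator) defines the endpoint: "The primary outcome measure is the total effective rate of the 8-week MoCA score". A patient counts as effective when the relative gain reaches 12%, where "Improvement rate = [(posttreatment score − pretreatment score)/pretreatment score] × 100" per cent. The endpoint is therefore binary and is computed from the baseline score.

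Section 2.6 (Sample size calculation) sizes the trial on the same proportion. Earlier work "reported a total effective rate of 13.72% for the 8-week MoCA score in the sham acupuncture group after treatment", and "We anticipated a total effective rate of 58.33% for the 8-week MoCA score post-treatment in the verum acupuncture group". With two-sided alpha 0.05, power 0.9 and 20% attrition, this gives 25 per group.

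Section 4 (Statistical analysis) then goes through its methods:
- Dichotomous data: "The chi-square test or Fisher’s exact test will be employed to compare dichotomous data from baseline demographic and clinical information".
- Description: "Categorical variables will be reported as medians (interquartile ranges".
- Scale scores and cytokines: "For normally distributed variables, an independent samples t-test will be used for between-group comparisons", with Mann–Whitney if the data are not normal and paired t-tests within groups.
- Multiple time points: repeated-measures ANOVA, and later GEE, with no outcome or covariate named for either.
- Regression: only to relate efficacy to cytokines.

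The intention-to-treat set requires a baseline assessment of the primary outcome and at least one treatment session.

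**The concern.** There are two defects, and they do not depend on each other.

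First, the comparison on which the trial is powered does not appear in the analysis section. Read literally, the efficacy tests run on scores, the dichotomous test runs on baseline characteristics, and the responder rate is summarised by a median. If the test is settled only when the data are in hand, a borderline result can turn on that choice.

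Second, baseline MoCA is available for everyone analysed, but no between-group efficacy comparison is said to adjust for it. For the scores, the method also depends on how the data look (t-test or Mann–Whitney), and two methods are named for the multi-visit comparison. The stake here is precision and pre-specification. The unadjusted comparison of randomised arms remains valid.

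**Working it through.** **Inputs from the protocol:** p1 = 0.1372 (sham), p2 = 0.5833 (verum), two-sided alpha 0.05, power 0.90, attrition 20%, 1:1 allocation. **Assumed, not in the protocol:** the baseline/week-8 MoCA correlation r, taken from 0.3 to 0.8.

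**Step 1. Reproduce the stated sample size.** Unpooled two-proportion formula:

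n = (1.960 + 1.282)² × [p1(1−p1) + p2(1−p2)] / (p2−p1)²
= 10.507 × (0.1184 + 0.2431) / 0.1990 = 19.08, so 20 per arm; 20 / 0.80 = 25 per arm.

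The planned figure is reproduced. It rests on a two-proportion comparison that Section 4 does not assign to the endpoint.

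**Step 2. Does the open choice of test matter?** Exact power by enumerating all pairs of binomial counts at the planned rates:

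| Evaluable per arm | Chi-square, uncorrected | Fisher | Chi-square, Yates |
|---|---|---|---|
| 20 | 0.877 | 0.801 | 0.773 |
| 25 | 0.941 | 0.890 | 0.890 |

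At 20 per arm no version reaches 0.90, and the spread is about 10 percentage points. A single table shows the consequence: 3/25 against 10/25 gives p = 0.024 by uncorrected chi-square and p = 0.051 by Fisher. Three sham responders is a realistic count, since 0.1372 × 25 = 3.4.

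**Step 3. What does baseline adjustment add for the responder rate?** Simulation with 40,000 trials per setting: bivariate normal baseline and week-8 scores, response defined as change above a threshold calibrated to the two planned rates, and a linear model with and without baseline.

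| r | Variance of responder difference, adjusted / unadjusted (20; 25 per arm) | Power at 20 per arm, unadjusted → adjusted |
|---|---|---|
| 0.3 | 0.845; 0.837 | 0.88 → 0.93 |
| 0.5 | 0.898; 0.899 | 0.88 → 0.91 |
| 0.7 | 0.949; 0.952 | 0.88 → 0.89 |
| 0.8 | 0.981; 0.972 | 0.88 → 0.88 |

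The saving runs from about 16% at r = 0.3 to 2–3% at r = 0.8.

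**Step 4. And for continuous scores?** The large-sample variance of ANCOVA relative to a change-score t-test is (1 − r²) / [2(1 − r)] = (1 + r)/2. This is 0.65, 0.75, 0.85 and 0.90 for r = 0.3, 0.5, 0.7 and 0.8, a saving of 35% down to 10%. Against a t-test on raw week-8 scores the ratio is 1 − r², but Section 4 does not say that its t-test uses raw week-8 scores, so the change-score figures are the fairer ones to cite.

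**The case against.** The strongest reply is that the intended comparison is obvious. The sample size fixes a two-proportion contrast, clinical information could loosely include response, GEE can model a binary outcome, and a condensed article may leave model detail to an analysis plan. Part of this stands: had the article merely been silent on the test, there would be little to raise. But it is not silent. It directs its dichotomous test to baseline data and gives a descriptive rule that cannot apply to a proportion. Even the generous reading leaves chi-square or Fisher open.

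A second reply is that unadjusted comparison of randomised arms is valid, so adjustment is a matter of efficiency. That is correct, and the second defect is put forward only on that footing.

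Some stronger readings are tempting but unsupported:
- That the missing test itself costs precision. It does not; only the missing covariate does.
- That a chance baseline imbalance passes undiminished into the result. The endpoint is change relative to baseline, and Mann–Whitney is described for changes, so baseline is already partly used.
- That the higher power of a comparison of scores measures what is lost here. That gap is the cost of dichotomising, and the fix below keeps the responder endpoint.
- That the paired t-tests are offered as evidence of efficacy. Section 4 lists them for before/after comparisons within groups and attaches no such claim.

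**Conclusion.** Both defects hold, with different weight. The unassigned primary test and the medians rule need correcting before analysis, because the open choice moves power between 0.77 and 0.88 at 20 evaluable per arm and can move a realistic table across 0.05. Those powers assume the planned response rates. The figure of 20 is the plan's own number after attrition; since missing values are to be imputed, the number analysed may be nearer 25, where the range is 0.89 to 0.94.

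The missing baseline covariate is an avoidable but partial loss: about 16% down to 3% of variance for the responder difference, and 35% down to 10% for scores against a change-score t-test, for r from 0.3 to 0.8. The protocol gives no r, and the responder figures rest on a normal model. At high r the gain for the primary endpoint is close to nil.

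**What to change.** 1. **Primary endpoint.** State one between-group comparison of the week-8 total effective rate, adjusted for baseline MoCA and reported as a risk difference with 95% CI, for example a standardised risk difference from a logistic model. Firth penalisation is optional; it pulls the estimated risk difference towards zero, so its use should be decided in advance.
2. **Sensitivity analysis.** Keep the unadjusted comparison, naming the exact test (uncorrected chi-square, Yates or Fisher), and state the power that the chosen test has at the planned number.
3. **Scores.** For MoCA, MMSE and QLQ-C30, replace the data-dependent choice among t-test, Mann–Whitney, repeated-measures ANOVA and GEE by one baseline-adjusted model: ANCOVA at week 8, or a mixed model over weeks 8 and 14.
4. **Description.** Report categorical variables as n (%) and skewed continuous variables as median (IQR).

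The cost is wording. No new data or visits are needed. ANCOVA and the mixed model run in SPSS; penalised logistic regression, if chosen, needs an add-on or another package. The Trial status section reports 20 of the planned 50 patients enrolled, so the change can be made before analysis.

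### The observed distribution picks the analysis of every continuous outcome, so weeks 8 and 14 of one outcome can end up on different tests and effect measures

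*Protocol article*

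**What the plan says.** Section 4 (Statistical analysis) first defines the variables concerned: "Measurement data include various scale scores and indicators of inflammatory cytokine expression levels". It then gives two routes.

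- **Normal:** "For normally distributed variables, an independent samples t-test will be used for between-group comparisons". The next sentence adds: "Comparisons at multiple time points will be made using repeated-measures analysis of variance".
- **Non-normal:** "The Mann–Whitney U test will be utilized for non-normally distributed variables in intergroup comparisons to analyze changes in efficacy outcomes". The sentence after it gives the comparison over several visits to generalized estimating equations, without saying for which variables. Only its position ties it to this route.

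Table 1 places MoCA, MMSE, QLQ-C30 and cytokines at baseline, week 8 and week 14. Section 2.6 plans 25 patients per arm, and section 2.7.2.3 takes cytokines from 15 per arm. Section 2.7.1 makes the primary outcome a rate of responders at week 8, so it is not a measurement variable in the sense of section 4.

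**The concern.** A rule that depends on whether a variable is normally distributed can only be applied by looking at the trial's own data. Three things follow.

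1. Each outcome has two arms and three visits. If it looks normal at week 8 and not at week 14, the rule sends it down both routes and does not say which prevails. The report could then show a mean difference at one visit beside a rank comparison at the other, and the two cannot be compared.
2. The scale scores are coarse and bounded ("The MoCA test has a maximum score of 30 points"), and the arms are small. For a score of this kind, the result of a normality check is largely chance.
3. Only the Mann–Whitney sentence names changes. The t-test sentence does not say whether levels or changes are compared.

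At stake is how the supportive cognitive, quality-of-life and cytokine results can be read. The cytokine results carry the trial's mechanistic aim.

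**Working it through.** **1. The plan's own figure.** Section 2.6 uses rates of 13.72% and 58.33% with "0.05 (two-sided) and a power of 0.9", and 20% attrition. With the unpooled two-proportion formula:

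n = (1.960 + 1.282)² × [0.1372 × 0.8628 + 0.5833 × 0.4167] / (0.5833 − 0.1372)² = 10.507 × 0.3614 / 0.1990 = 19.08, so 20 evaluable per arm; 20 / 0.80 = 25.

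The stated 25 per arm reproduces. It belongs to the binary primary outcome, which the normality rule does not touch. The plan gives no SD, correlation or power for any continuous outcome, so every input below is an assumption.

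**2. How often the two visits split.** Assume a Shapiro-Wilk test at 5% in each arm, with the t-test used only if both arms pass. Let p be the chance of passing at one visit. If the visits were independent, the chance of a split would be 2p(1 − p).

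| Case | p | 2p(1 − p) | Simulated split |
|---|---|---|---|
| Exactly normal data, 25 per arm | 0.95² = 0.9025 | 0.176 | 0.18 |
| MoCA-like integer score, 25 per arm | 0.68 | 0.435 | 0.43 |
| MMSE-like score with ceiling, no effect, 25 per arm | 0.24 | 0.365 | 0.33 |
| Strongly skewed cytokine levels, 15 per arm | 0.03 | 0.058 | 0.06 |

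Splitting is most frequent when normality is in doubt and rare when the data are plainly skewed. Across the settings tried, the MoCA-like score split in about 35–45% of trials. Log-normal cytokines split in 28–42% when changes were checked (log SD 0.3–0.8). When levels were checked they split in 16% (log SD 0.8) and 5% (log SD 1.0). The MMSE-like score with an assumed 0.8 SD effect almost always failed the check, so it split in only 0.3%.

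**3. Type I error.** Followed mechanically, the rule gave about 0.045–0.055.

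**4. Power, scale scores.** MoCA-like score, 25 per arm, assumed effect 0.8 SD, at week 8:

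| Pre-post correlation | Always t on level | Rule, level in both branches | Rule, level if normal, change if not | Baseline-adjusted model |
|---|---|---|---|---|
| 0.3 | 0.801 | 0.787 | 0.746 | 0.822 |
| 0.5 | 0.769 | 0.760 | 0.762 | 0.866 |
| 0.6 | 0.785 | 0.779 | 0.805 | 0.915 |
| 0.8 | 0.788 | 0.782 | 0.848 | 0.988 |

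With one quantity throughout, the check costs 0.6 to 1.4 points. If the quantity switches with the branch, the rule loses 5.5 points at correlation 0.3 (0.801 − 0.746) and gains 6.0 at 0.8 (0.848 − 0.788). The advantage of the last column comes from baseline adjustment, not from dropping the check.

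A second set assumed a 1.5-point MoCA effect and a change SD of 2. It compared the switching rule with a t-test on change, for three assumed slopes of the week-8 score on baseline:

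- slope 1: 56% v 73%
- slope 0.5: 64% v 63%
- slope 0.3: 67% v 60%

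With changes in both branches (slope 1), both had 72%.

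**5. Power, cytokines.** Log-normal values, 15 per arm, changes in both branches, assumed effect 0.8 log SD. At log SD 0.5 and correlation 0.6, the rule on raw values had 52% power and a t-test on log change 67%, a gap of 15 points. Across the settings tried the gap was about 6–27 points, growing with skewness. These gaps apply to a cytokine that verum lowers. In a rerun with a rise of the same size, the loss against log change was small or absent.

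**The case against.** The strongest reply is that this is a clarity point about secondary outcomes. The choice of normality test, its threshold and whether it is repeated at each visit are details that an article may leave to an analysis plan. The per-visit, per-arm Shapiro-Wilk check is an assumption made here. Both points stand, and they limit how far the percentages can be trusted. But the article does state the rule, and an analysis plan that carried it out would inherit the gap.

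Three stronger readings are tempting, and the document does not support them.

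- **That the primary result is at risk.** It is not: the primary outcome is a binary rate outside this rule.
- **That the compared quantity switches from level to change with the branch, so that MoCA loses power.** The wording allows this, but changes may be meant for both tests: section 2.7.1 says that changes in MoCA will assess cognitive function, with no condition on normality. Even on the literal reading, the loss depends on the pre-post relation and can reverse.
- **That the rule inflates false positives.** Picking the better of two p-values would raise the error to about 6% (both on change) or 8% (level against change). Nothing says that both will be run, and section 4 assigns the analysis to an independent statistician blinded to group.

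It is also fair that for markedly skewed cytokine levels the rule usually gives the same answer at both visits.

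**Conclusion.** The point holds for the continuous MoCA score, MMSE, QLQ-C30 and cytokines. The stated rule does not determine one analysis, one effect measure or, on its wording, one compared quantity per outcome. That conclusion needs no simulation.

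Its size rests on the assumed check, SDs, correlations and distributions: visits on different tests in about 35–45% of trials for a MoCA-like score and about 5–40% for cytokines. The harm is mainly to interpretation. Error rates are not inflated if the rule is followed, and no MoCA power loss can be claimed in general. The one clear power cost is for skewed cytokines kept on the raw scale, about 6–27 points where verum lowers the cytokine. The plan should be changed, but the trial's main test does not depend on it.

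**What to change.** Before unblinding, delete the normality-dependent choice from section 4, or override it in the analysis plan. For each continuous outcome name one quantity and one model, the same at weeks 8 and 14:

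- **MoCA, MMSE and QLQ-C30 scores:** between-arm mean difference with 95% CI from a linear model of the follow-up score adjusted for its baseline value, whatever the observed distribution.
- **Cytokines:** the same model on the log scale.
- **All visits together:** one named multi-visit model, in place of repeated-measures ANOVA for some variables and GEE for others.
- **Mann–Whitney on the change from baseline:** kept as a labelled sensitivity analysis.

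This needs no new patients or data. Section 5 reports 20 of the planned 50 patients enrolled and recruitment continuing, so the change can still be made in time. The small downside is that a skewed score is summarised by a mean in the main analysis; the rank-based sensitivity analysis covers that.

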## Trial status

5

The Medical Ethics Committee of Beijing Hospital of Traditional Chinese Medicine, Capital Medical University, China, granted approval for this study on 9 January 2024. Currently, the trial is in the recruitment phase, which is scheduled to continue until May 2026. As of now, 20 patients have been enrolled, with the initial participant joining on 19 February 2024.

## Discussion

6

CRCI represents a significant and prevalent issue for breast cancer survivors, adversely affecting their quality of life (32). While CRCI in breast cancer patients undoubtedly warrants increased attention, there is currently no established principle or guideline for its management. This single-blind, randomized, controlled trial aims to evaluate the efficacy and safety of acupuncture in treating CRCI in TNBC patients, while also exploring the potential mechanisms underlying this treatment approach. Acupuncture, a traditional Chinese medical therapy, has emerged as a promising intervention for mild cognitive impairment. Multiple studies have demonstrated acupuncture’s efficacy in enhancing cognitive function across various pathological conditions (43–45). Our previous research, employing the principle of “reconciling qi and blood, tonifying heart and mind,” has substantiated the effectiveness and safety of acupuncture for breast cancer patients experiencing CRCI (17, 46). This study specifically focuses on TNBC patients due to their higher incidence of CRCI and its consequential impact on quality of life. To the best of our knowledge, no studies have yet investigated the efficacy of acupuncture in managing CRCI among TNBC patients.

Chemotherapy has been observed to elevate the levels of inflammatory mediators such as IL-1β, TNF-*α*, and COX-2, while simultaneously reducing the levels of the anti-inflammatory cytokine IL-10 (47). These inflammatory factors can induce neuroinflammation and contribute to cognitive impairment. Given the crucial role of inflammatory factors in the development of CRCI, this study also measured serum inflammatory factor levels. This approach allows for an exploration of the therapeutic mechanism of acupuncture in treating CRCI.

This randomized, sham-acupuncture-controlled study was primarily designed to investigate the efficacy and safety of acupuncture in managing CRCI among TNBC patients and provide physicians with evidence-based guidelines for treating CRCI. Furthermore, this trial aims to explore the mechanisms through which acupuncture may exert its therapeutic effects in breast cancer patients with CRCI, potentially offering new insights into its therapeutic efficacy.

Nevertheless, the current study design has certain limitations. In this trial, the sham acupuncture group uses a non-meridian and non-acupoint needling approach where shallow needling is performed on superficial skin to minimize stimulation and avoid inducing the arrival of qi sensation. However, it cannot be guaranteed that sham acupuncture will have no therapeutic effect on the disease. Recent studies on the non-penetration of the sham needles have yielded inconsistent results. Some researchers contend that superficial needling can produce specific acupuncture effects, resulting in false negatives (48). Studies have shown that the responses to tactile stimulation such as skin compression or prickling sensations may elicit certain physiological responses in the body and activate the somatosensory system and relevant brain regions and thereby produce specific effects (49, 50). However, recent research suggests that skin-penetrating sham needles can be used as inert placebo controls in randomized controlled trials (51). In conclusion, the potential for physiological effects arising from the control group’s design cannot be disregarded. Previous randomized controlled trials have demonstrated that superficial insertion may elicit physiological responses that alleviate symptoms. Although this study will select sham points to avoid meridians and acupoints, the possibility of distinct physiological effects in the control group cannot be entirely eliminated. Another primary limitation is the inability to blind the treating therapists. Achieving true double-blind conditions in acupuncture trials is practically unfeasible, as acupuncturists manage participants’ perceptions of needling. Consequently, differentiating between the actual impact of acupuncture and placebo or physiological effects remains challenging. The potential for bias due to the lack of blinding cannot be excluded. Additionally, in the context of a chronic disease such as CRCI, a 6-week assessment period may be inadequate for gaining a thorough understanding. To draw definitive conclusions regarding the long-term impact of acupuncture interventions, additional real-world studies involving extended follow-up periods are essential.
